# SCREENING AND ENROLLMENT PROCEDURES

**Screening Procedures for Enrollment**

Screening for eligible patients at the three study sites will be done in the following fashion:

1. All patients presenting to Adama Malaria Training Center and Debrezeit Malaria Center will be registered. All patients routinely have microscopy performed prior to clinical evaluation by a laboratory technician. Patients aged over 6 months with microscopy confirmed Pf or Pv who live within 20 km of the health facility will be screened.

2. All patients with temperature ≥37.5oC or a history of fever in the last 48 hours will have screening blood smear performed as per the national diagnosis and treatment guidelines at Awash Melkasa Health Center. Patients with microscopy confirmed Pf or Pv, age greater than 6 months, and living within 20 km of the health center will be screened.

3. For all facilities, if the patient meets the screening criteria and the patient or the parent or guardian asked for permission consents to enrollment, they will be assigned a consecutive, unique number that will become the patient's study number and will be used to identify all forms and blood samples from that patient. Enrollment will be conducted by a staff member not involved in the clinical assessment of the participant to ensure that consent is freely given.

4. A screening form containing demographic, clinical, and laboratory information will be started on each smear positive patient, thus allowing for appropriate tracking of each patient through the screening procedure.

5. The patient’s body weight will be measured, using a hanging scale for weighing young children, or a floor scale for large children/ adults and recorded on the demographic form.

**Enrollment Procedures**

If a patient meets the initial screening criteria and permission to participate in the study is obtained, the patient will go through the enrolling process.

1. Patient will be evaluated by clinical staff for signs of febrile illness other than malaria, (including but not limited to pneumonia, otitis media, tonsillitis, measles, chicken pox, abscesses) and signs of severe disease/ danger signs, as presence of any of these will exclude the patient from participating in the study. Patients found to have any of these conditions will be treated appropriately per National Guidelines, and referred to the referral hospital as necessary. A standardized form listing demographic and clinical information will be completed on each patient.

2. Urine pregnancy test will be conducted on all women aged 13-49. Anyone testing positive will be excluded.

3. Those enrolled will have a second finger prick performed to assess for the following:

● Thin smear will be used to verify parasite species and to conduct a formal parasite count. Two microscopists will independently read each smear (one at the study site and the other at Adama Reference Laboratory); if the 2 readings are >20% discordant, a third expert microscopist at the Oromia Regional Laboratory will examine the slide and make the final decision.

- Hemoglobin measurement (Hemocue™ Hb201+; HemoCue, Angelholm, Sweden) will be carried out and those with hemoglobin <5g/dL will be excluded.
- Filter paper will be obtained for molecular testing and drug levels.

4. Consecutive patients testing positive for Pf will be enrolled and treated with AL if they meet all inclusion criteria. Patients testing positive for Pv will be randomized to either CQ or AL treatment arms. A permuted block randomization technique will be used to ensure equal numbers in the two treatment arms. The study will not be blinded, although microscopists reading blood films will not be aware of which arm a participant is from.

5. After assignment, on day 0, each patient will receive the morning dose of treatment medication under direct observation and will be monitored for vomiting. The patient or parent will be given the evening dose (for AL only) to administer at home. Each patient will return on days 1 and 2 for subsequent doses. Clinical reassessments will be made on days 1- 3, 7, 14, 21, 28, 35, and 42 (see Annex V for a table of scheduled procedures). Participants will be given 35 Ethiopian Birr for each visit to cover their travel expenses (this is enough to cover round-trip transportation by bus to the clinic for one adult; parent traveling with the enrolled child requiring their own seat (age >6 years) will receive 50 Birr). Patients will be advised to return on *any* day during the follow-up period if symptoms return and not to wait for scheduled visit days. Patients who do not present to the facility for follow-up visits will be followed at home. This is standard for in vivo studies based on the WHO protocol, but is not the standard for routine care. Typically, for patients not enrolled in a study, the parent would be given all the doses of the medicine to administer at home, and no follow-up would be scheduled. The parent would be told to return if the child did not improve.

6. Blood films (thick and thin) for parasite count will be obtained and examined at each visit except day 1 and on any other day if the patient spontaneously returns with fever or worsening symptoms. Hemoglobin status will be measured on days 0, 7, 14, 21, 28, 35, and 42. A filter paper blood spot will be collected on days 0 and in case of treatment failure. All molecular testing will be conducted in Addis Ababa, Ethiopia, by Ethiopia Health and Nutrition Research Institute (EHNRI). Blood drug level testing capacity does not currently exist in Ethiopia and will be conducted at CDC Atlanta. All samples will have the study ID number and date of collection, but no other personal identifiers. The logbook that links the study ID number to the patient will be kept at the study site locked in a cabinet when not in use during the study enrollment period. After the completion of the study, this logbook will be stored in a locked cabinet in Addis Ababa at the International Center for AIDS Care and Treatment Program’s office.

# FOLLOW-UP PROCEDURES

**Study Instruments**

Standard operating procedures and structured forms for clinical history, physical assessment, and data collection in English will be used by each study site. All study staff are familiar with English and health systems data collection in the country are routinely done in English.

# END-POINTS

**Outcomes and minimal differences**

The primary outcome of this study will be to estimate the efficaciousness of artemether-lumefantrine against falciparum malaria and vivax malaria and chloroquine against vivax malaria.

The classification of treatment outcomes will be based on an assessment of the parasitological and clinical outcome of antimalarial treatment according to the latest guidelines from WHO. Accordingly, all Pf patients will be classified as having an Early Treatment Failure (ETF), a Late Clinical Failure (LCF), a Late Parasitological Failure (LPF), or an Adequate Clinical and Parasitological Response (ACPR).

**Classification of Treatment Outcomes, WHO 2003**

**Early Treatment Failure (ETF)**

- Development of danger signs or severe malaria on day 1, day 2 or day 3 in the presence of parasitemia
- Parasitemia on day 2 higher than day 0 count irrespective of axillary temperature
- Parasitemia on day 3 with axillary temperature ≥37.5 ºC
- Parasitemia on day 3 ≥25% of count on day 0

**Late Treatment Failure (LTF)**

***Late Clinical Failure* (LCF)**

- Development of danger signs or severe malaria after day 3 in the presence of parasitemia, without previously meeting any of the criteria of Early Treatment Failure
- Presence of parasitemia and axillary temperature ≥37.5 ºC or history of fever on any day from day 4 to day 28 or 42, without previously meeting any of the criteria of Early Treatment Failure

***Late Parasitological Failure* (LPF)**

- Presence of parasitemia on any day from day 7 to day 28 or 42 and axillary temperature <37.5 ºC, without previously meeting any of the criteria of Early Treatment Failure or Late Clinical Failure

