**Adequate Clinical and Parasitological Response (ACPR)**

- Absence of parasitemia on day 28 or 42 irrespective of axillary temperature without previously meeting any of the criteria of Early Treatment Failure or Late Clinical Failure or Late Parasitological Failure

In order to differentiate a recrudescence (same parasite strain) from a newly acquired infection (different parasite strain), a genotypic analysis based on merozoite surface protein-1 (*msp1)*, merozoite surface protein 2 (*msp2)* and glutamate-rich protein (*glurp)* will be performed by PCR for Pf. Additionally, we will characterize microsatellite markers for Pf to differentiate recrudescence from reinfection and potentially assess for drug resistance markers.

**Definition of Treatment Outcomes for *P. vivax* infections, WHO 2002** [4]

Treatment failure defined as:

1. Clinical deterioration due to *P. vivax* illness requiring hospitalization in presence of parasitemia
2. Presence of parasitemia and axillary temperature ≥37.5oC any time between Day 3 and Day 28 or 42
3. Presence of parasitemia on any day between day 7 and day 28 or 42, irrespective of clinical conditions.

*P. vivax* infections that recur after drug treatment can have 1 of 3 etiologies: 1) recrudescence, 2) reinfection, or 3) relapse arising from the dormant liver stage (hypnozoites). In order to differentiate the treatment failures as recrudescence or relapse from a newly acquired infection, a genotypic analysis based on P. vivax circumsporozoite protein (*pvcs*), the merozoite surface protein 1 (*pvmsp1*) and the merozoite surface protein 3-alpha (*pvmsp3-alpha*) will be performed by PCR for Pv. Additionally, we also will characterize microsatellite markers to assess recrudescence from reinfection and for drug resistance markers. Those who fail in the vivax arms will have drug levels tested from the already collected filter paper.

**Valid end-points** include treatment failure, completion of the follow-up period without treatment failure, loss to follow-up, withdrawal from study (voluntary or involuntary, and protocol violation). Loss to follow-up occurs when, despite all reasonable effort, an enrolled patient who does not attend the scheduled visits, cannot be found. Patients who withdraw from the study during the treatment period (days 0-2) will be treated with AL or CQ depending on the species according to the national policy. They will be referred back to the clinic to continue with care.

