**Criteria for withdrawal**

Patients meeting any of the following criteria will be withdrawn:

- Withdrawal of consent
- Failure to complete the treatment
- Vomiting both initial and replacement doses at any single time in the treatment (i.e. If the patient vomits both attempts to administer the morning dose that would require withdrawal; however, vomiting the initial morning dose but not the morning replacement dose would not require withdrawal), persistent vomiting
- Severe side-effects necessitating hospitalization
- Progression to severe malaria
- Occurrence during the follow-up of concomitant disease that would interfere with a clear classification of the treatment outcome
- Antimalarial (or antibiotics with antimalarial activity) treatment administered by a third party or self-medication with antimalarial (or antibiotics with antimalarial activity) assessed by asking participants or their caretaker at follow-up visits
- Detection of another malaria species infection during the follow-up
- Erroneous inclusion of a patient outside of the inclusion/exclusion criteria
- Misclassification of a patient due to a laboratory error (parasitemia) leading to the administration of the rescue treatment

**Training for personnel**: Clinicians and laboratory personnel are trained and licensed in Ethiopia. In addition, they will receive approximately 1 week additional training to review the protocol of this study. In addition to technical aspects of specific laboratory techniques and clinical assessments, training will stress the importance of confidentiality, appropriate techniques for obtaining informed consent, Staff will participate in practical exercises. Continued appropriate behavior with regard to informed consent will be reinforced by intermittent observation by the supervisor. The staff will include 1-2 laboratory technicians for microscopy, and 1-2 staff persons for enrollment and clinical assessments.

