# DATA HANDLING AND ANALYSIS

**Data analysis plan, including statistical methodology and planned tables and figures**

SAS 9.1 (Cary, NC) as well as the WHO drug efficacy tools provided at <http://www.who.int/malaria/toolsformonitoring.html> will be used for data management and analysis. Data will be analyzed using two methods: **per protocol analysis**, where patients who were withdrawn from the study or who were lost to follow-up are excluded, and **survival analysis**, where all enrolled patients are included in the analysis until the last day before drop-out. In addition to voluntary withdrawals or treatment non-compliance, patients will be considered for the analysis as withdrawn if the PCR results are unclassifiable.

The final analysis will include:

- A description of the patients screened, and the distribution of the reasons for exclusion.
- A description of the patients included in the study.
- The proportion of patients lost to follow-up or withdrawn and the distribution of reasons for withdrawal.
- The PCR-adjusted and unadjusted proportion of ETF, LCF, LPF, and ACPR in the Pf arm at day 28 and day 42 with 95% confidence intervals using both methods of analysis.
- Both drug-level and PCR-adjusted and unadjusted proportion of treatment failures in each Pv arm at day 28 and day 42 with 95% confidence intervals using both methods of analysis
- Frequency of side effects, severe malaria, anemia, and hospitalizations by treatment arm

**Data collection**: Data will be collected and recorded at the health facility by one of the trained staff members. All data entry forms will be checked for completeness. Laboratorians may complete brief reports on laboratory findings to share with clinicians who will transfer these results to the case report form of the appropriate patient, the laboratory results will be entered into an Excel database.

**Information management and analysis software:** Microsoft Excel (Redmond, Washington) will be used for double entry of laboratory data and clinical data. SAS 9.1 (Cary, NC) will be used for data analysis.

**Data entry, editing, handling, storage and disposition**: Some open-ended data including the names of specific drugs or diagnoses will be coded prior to data entry. A list of standard codes for these fields will be developed by hand once collection of data is complete. All forms will then be coded and checked by 2 different team members.

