### ANNEX II *P. vivax* treatment outcomes

| **Definition of treatment outcomes for vivax malaria**  **WHO [4]** |
| --- |
| **Treatment Failure (TF)** |
| - Clinical deterioration due to *P. vivax* illness requiring hospitalization in presence of parasitemia - Presence of parasitemia and axillary temperature ≥37.5oC any time between Day 3 and Day 28 or Day 42 - Presence of parasitemia on any day between day 7 and day 28 or day 42, irrespective of clinical conditions |

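### Withdrawal on detection of another species has no exception for mixed recurrences, so a genuine return of the treated species can be counted as a failure in neither analysis

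*Protocol*

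**What the plan says.** **Outcome definitions, P. falciparum (END-POINTS and Annex I).** Late clinical failure is "Presence of parasitemia and axillary temperature ≥37.5 ºC or history of fever on any day from day 4 to day 28 or 42". Late parasitological failure is "Presence of parasitemia on any day from day 7 to day 28 or 42 and axillary temperature <37.5 ºC". Adequate clinical and parasitological response (ACPR) requires "Absence of parasitemia on day 28 or 42 irrespective of axillary temperature". None of these criteria names a species.

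**Outcome definitions, P. vivax (END-POINTS and Annex II).** The first criterion names a species, but for the illness: "Clinical deterioration due to *P. vivax* illness requiring hospitalization in presence of parasitemia". The second and third speak of parasitemia only; the third is "Presence of parasitemia on any day between day 7 and day 28 or 42, irrespective of clinical conditions".

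**Criteria for withdrawal.** Withdrawal is mandatory for any listed reason, and one of them is "Detection of another malaria species infection during the follow-up". It is not limited to cases where the other species appears alone.

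**Valid end-points.** Treatment failure and withdrawal are listed as separate end-points. Nothing says which applies when a patient meets both.

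**Data analysis plan.** The per-protocol analysis is the one "where patients who were withdrawn from the study or who were lost to follow-up are excluded". The survival analysis includes everyone enrolled, but only up to the day before they drop out.

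**The concern.** A patient treated for P. falciparum whose P. falciparum returns together with P. vivax is a failure under any reading of the outcome criteria. The same slide also triggers mandatory withdrawal. If withdrawal governs, the event disappears from the per-protocol numerator and denominator, and the survival analysis censors the patient just before the event. The mirror case arises in both vivax arms. The loss runs in one direction only: failures are removed and successes are not, so estimated efficacy rises. Efficacy of each drug is the primary outcome.

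A second, lesser problem concerns an infection with the other species alone. Because the criteria name no species, it literally meets both a failure definition and a withdrawal criterion.

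The setting makes both events plausible. The Introduction describes the two species as co-dominant in the country, with relative frequencies of 60% and 40%. It also says that neither drug acts on the liver stage of P. vivax, which can cause relapse weeks later. Excluding mixed infection on the enrollment slide does not rule out a mixed picture later.

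**Working it through.** **1. The plan's own precision figure.** The sample-size section assumes 90% ACPR, 120 patients per arm and 20% loss, and states an exact 95% interval of 82.4% to 95.1%. The Clopper-Pearson interval for 90/100 is 82.4% to 95.1%, so the figure reproduces; 100 evaluable corresponds to 120 through 100 × 1.2. Taking the 20% loss from 120 gives 120 × 0.8 = 96 evaluable, and 86/96 gives 81.7% to 94.9%, almost the same. The stated half-width is (95.1 − 82.4)/2 = 6.35, about 6 points. This figure is not in dispute; it is the yardstick.

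**2. What each rule does to each kind of recurrence (P. falciparum arm).**

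| Finding in follow-up | Outcome criteria, literal reading | Withdrawal list | Per protocol if withdrawn | Survival if withdrawn |
|---|---|---|---|---|
| P. falciparum alone | Failure | Not triggered | Not applicable | Not applicable |
| P. falciparum with P. vivax | Failure | Triggered | Excluded | Censored the day before; event lost |
| P. vivax alone | Failure literally; headings suggest not | Triggered | Excluded | Censored the day before |

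The second row is the substantive defect. The third is a conflict of wording.

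**3. Size of the mixed-recurrence effect.** Let S be responders, F all failures by the treated species, and m the failures that are mixed and therefore withdrawn.

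- Kept as failures: ACPR = S/(S + F)
- Withdrawn: ACPR = S/(S + F − m), which is larger whenever m > 0

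With S = 86 and F = 10 (96 evaluable, about 10% failure as the plan assumes):

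| m (assumed) | ACPR if withdrawn | Shift from 86/96 = 89.6% | Exact 95% interval |
|---|---|---|---|
| 1 | 86/95 = 90.5% | +0.9 | 82.8% to 95.6% |
| 2 | 86/94 = 91.5% | +1.9 | 83.9% to 96.3% |
| 5 | 86/91 = 94.5% | +4.9 | 87.6% to 98.2% |

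The values of m are assumptions, because the documents give no rate of mixed recurrence. In the survival analysis the direction is the same, since m events become censored observations.

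**The case against.** The strongest reply is that the criteria take their species from context. The outcome section classifies P. falciparum patients under a falciparum heading, Annex I is titled for falciparum malaria, and the vivax criteria sit under a vivax heading. The genotyping text treats recurrences as same-species events, with P. falciparum markers for one group and P. vivax markers for the other. The withdrawal list then supplies a specific rule for another species. Read together, an infection with the other species alone is a withdrawal. This largely stands.

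A reader might infer more from the silence on species: that other-species infections will be charged to the study drug and pull reported efficacy well down. The documents do not support that. It would require staff to set the withdrawal rule aside, and no 42-day rate of such infections is given. The site table does not supply one: it reports clinic case counts, and at Awash Melkassa P. falciparum exceeds P. vivax in both periods shown (171 against 163, and 42 against 14). For PCR-adjusted results, other-species-alone cases might also fall under the rule that treats unclassifiable PCR as withdrawal.

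A reader might also infer a biased comparison of the vivax arms, since the protocol says that resistance made chloroquine ineffective against P. falciparum while artemether-lumefantrine is its treatment. That is secondary: the analysis plan lists per-arm proportions and no between-arm test, and the Limitations section says that the study is not powered for arm differences.

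It can also be said that precedence between simultaneous events is often left to a statistical analysis plan, that the survival analysis keeps the patient's earlier follow-up, and that a shift of 1 or 2 points is well inside the planned half-width. These points limit the size. They do not answer the mixed case: the context that rescues the other-species-alone reading does nothing for a recurrence that contains the treated species, and the protocol itself makes withdrawal mandatory there.

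**Conclusion.** The point holds for mixed recurrences. As written, the protocol withdraws a patient whose treated species has returned if the other species is seen as well, and neither planned analysis then counts the failure. The direction is certain if the withdrawal rule governs: efficacy is overstated. The size is unknown. It is about 1 to 2 points of ACPR for one or two such patients in 96, and about 5 points, close to the planned half-width, if half of 10 failures were mixed. It rests on assumed counts and on withdrawal taking precedence, which its mandatory wording implies but no passage states.

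The missing species in the outcome definitions is a conflict of wording, and context favors withdrawal for infections with the other species alone. Overall this is a moderate defect in the classification of the primary outcome, worth correcting because correction is cheap.

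**What to change.** Reconcile the END-POINTS section, Annexes I and II, the withdrawal list and the analysis plan, for outcome classification only:

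- In the failure and ACPR definitions, name the species treated on day 0 (P. falciparum parasitemia or P. vivax parasitemia).
- Count a mixed recurrence that contains the day-0 species as a treatment failure on the day it is found. For the PCR-adjusted result, let genotyping of the day-0 species classify it like any other recurrence.
- Limit the other-species withdrawal criterion to infections without the day-0 species. Exclude these per protocol, censor them at detection in the survival analysis, and report their number by arm.
- State that treatment failure takes precedence when both are met on the same day.

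The cost is wording in the endpoint section, two annexes and one withdrawal criterion. Slightly more failures will be reported where recurrences are mixed. Species must be recorded on follow-up slides; the protocol spells out species verification only for the enrollment smear, but the existing withdrawal criterion already presupposes it later.
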